## LIST OF ABBREVIATIONS AND RELEVANT DEFINITIONS

|                |                                                                                                                                                                                                                                                                                                                                                  |
|----------------|--------------------------------------------------------------------------------------------------------------------------------------------------------------------------------------------------------------------------------------------------------------------------------------------------------------------------------------------------|
| AE      | Adverse Event                                                                                                                                                                                                                                                                                                                             |
| AR      | Adverse Reaction                                                                                                                                                                                                                                                                                                                          |
| CA      | Competent Authority                                                                                                                                                                                                                                                                                                                       |
| CBO     | Dutch Institute for Healthcare Improvement                                                                                                                                                                                                                                                                                                |
| CCMO    | Central Committee on Research Involving Human Subjects; in Dutch: Centrale Commissie Mensgebonden Onderzoek                                                                                                                                                                                                                               |
| CEA     | Cost effectiveness analysis                                                                                                                                                                                                                                                                                                               |
| CV      | Curriculum Vitae                                                                                                                                                                                                                                                                                                                          |
| DSMB    | Data Safety Monitoring Board                                                                                                                                                                                                                                                                                                              |
| EU      | European Union                                                                                                                                                                                                                                                                                                                            |
| GCP     | Good Clinical Practice                                                                                                                                                                                                                                                                                                                    |
| IC      | Informed Consent                                                                                                                                                                                                                                                                                                                          |
| IGZ     | Health Care Inspectorate                                                                                                                                                                                                                                                                                                                  |
| iMCQ    | Medical Consumption Questionnaire                                                                                                                                                                                                                                                                                                         |
| IPCQ    | Productivity Cost Questionnaire                                                                                                                                                                                                                                                                                                           |
| METC    | Medical research ethics committee (MREC); in Dutch: medisch ethische toetsing commissie (METC)                                                                                                                                                                                                                                            |
| NAAP    | Non-Anesthesiologist Administered Propofol                                                                                                                                                                                                                                                                                                |
| PBAC    | Pictorial Blood Assessment Chart                                                                                                                                                                                                                                                                                                          |
| PSA     | Procedural sedation and analgesia                                                                                                                                                                                                                                                                                                         |
| RCT     | Randomized Controlled Trial                                                                                                                                                                                                                                                                                                               |
| (S)AE   | (Serious) Adverse Event                                                                                                                                                                                                                                                                                                                   |
| SF-HLQ  | Short Form-Health and Labour Questionnaire                                                                                                                                                                                                                                                                                                |
| Sponsor | The sponsor is the party that commissions the organisation or performance of the research, for example a pharmaceutical company, academic hospital, scientific organisation or investigator. A party that provides funding for a study but does not commission it is not regarded as the sponsor, but referred to as a subsidising party. |
| SUSAR   | Suspected Unexpected Serious Adverse Reaction                                                                                                                                                                                                                                                                                             |
| TVU     | Transvaginal Ultrasonography                                                                                                                                                                                                                                                                                                              |
| UFS-QoL | Uterine Fibroid Symptoms – Quality of Life questionnaire                                                                                                                                                                                                                                                                                  |
| WMO     | Medical Research Involving Human Subjects Act (in Dutch: Wet Medisch-wetenschappelijk Onderzoek met Mensen)                                                                                                                                                                                                                               |

## SUMMARY

**Rationale:** Hysteroscopic myomectomies are performed in the majority of Dutch hospitals. The number of procedures for submucosal type 0 or I myomas between 1-3 cm performed in the operating room is estimated to be 3000 per year. Hysteroscopic myomectomy is currently performed in daycare under general anesthesia. A considerable cost reduction is expected when procedural sedation (PSA) is applied. The major contributing factors to the cost reduction are the shift from surgery in an operating theatre to an office-based setting, shorter hospital stay and outpatient care versus day care. We expect higher patient satisfaction, as hospital stay is shorter and side effects such as nausea are reduced. However, both safety and effectiveness – including the necessity for re-intervention due to incomplete resection – have not yet been fully evaluated.

**Objective:** Is hysteroscopic resection of submucous myomas under procedural sedation with propofol (PSA) in an outpatient setting a cost-effective alternative for hysteroscopic myomectomy performed under general anesthesia in the operation room?

**Study design:** non-inferiority, multicenter RCT, with a cost effectiveness analysis (CEA) alongside it.

**Study population:** patients with submucosal type 0 or I myomas (FIGO (PALM COEIN)) with a maximum diameter of 3 cm. We use a non-inferiority design: based on estimated risk of 2,5% incomplete resections in both groups, with an non-inferiority upper limit of 10%, 205 women are needed.

**Intervention:** hysteroscopic resection of submucous myomas under procedural sedation with propofol, compared to general anesthesia

**Main study parameters/endpoints:** 1) complete resection 2) costs, pain, menstrual blood loss (PBAC score), , quality of life, return to daily activities/work, hospitalization, (post)operative complications, re-interventions.

**Nature and extent of the burden and risks associated with participation, benefit and group relatedness:** Patients participating in this study are requested to complete a questionnaire at baseline, after 24 hours, 2 weeks, 8 weeks, 6 months and 12 months after the procedure. At 6 weeks after the procedure patients are asked to visit the outpatient department for a transvaginal ultrasound to assess the completeness of resection. This visit is part of the current usual care.

## 1. INTRODUCTION AND RATIONALE

Myomas are a frequent finding in patients with abnormal uterine bleeding. Hysteroscopic resection of submucosal myomas is an effective therapeutic intervention in case of heavy menstrual bleeding which is performed in an estimated 3000 women annually in the Netherlands. This number is extrapolated from data obtained from annual reports of 15 Dutch hospitals (teaching and non-teaching hospitals). A success rate (reduction of symptoms) of 70-99% has been reported [1-6]; the wide range reflects inclusion of all types of submucous myomas, also intramural myomas (FIGO PALM-COEIN type 2 submucous myomas) in the studies. The Dutch guideline on Heavy Menstrual Bleeding recommends hysteroscopic myomectomy as a first choice treatment in case of submucosal myomas. In the last decades, there has been a trend in hysteroscopic surgery to move from a traditional operating theatre with general anesthesia to an outpatient setting. This trend has specifically been observed for hysteroscopic surgery of smaller diameter polyps (< 2 cm) and low grade adhesions [7-9]. Even for smaller type 0 and 1 submucosal myomas it has been reported that these can successfully be removed in an outpatient setting without anesthesia[10]. Larger myomas generally require the use of a larger diameter instrument and hence the need of cervical dilatation and general anesthesia.

Procedural sedation is used for a wide variety of interventional procedures in multiple settings outside the operation room. There is literature examining safety and efficacy of procedural sedation during gastrointestinal endoscopic procedure, emergency department procedures and pediatric sedation. [11-15].

In gynecology, the use of procedural sedation has also become more popular since technical and instrumental improvements have significantly increased the feasibility and acceptability of hysteroscopy in outpatient settings [16-17]. For resection of myomas, procedural sedation is currently not commonly used. Potential advantages of hysteroscopic resection of myomas with procedural sedation are avoidance of general anesthesia and its associated risks and side effects, a shorter recovery time, a shorter hospital stay and return to mobility and full fitness, faster return to normal activities and work, lower costs related to decreased use of dedicated personnel and operating room, and reduced waiting lists for major surgery by averting the need for the operating room for minor procedures [18].

**HEALTH CARE EFFICENCY PROBLEM:** Hysteroscopic myomectomies are performed in the majority of Dutch hospitals. The number of procedures for submucosal type 0 or I myomas between 1-3 cm performed in the operating room is estimated to be 3000 per year. This number is extrapolated from data obtained from annual reports of 15 Dutch hospitals (teaching and non-teaching hospitals). Hysteroscopic myomectomy is currently performed in

daycare under general anesthesia. A considerable cost reduction is expected when procedural sedation is applied. The shift from surgery in an operating theatre to an office-based setting and shorter hospital stay -day care versus outpatient care- are the major contributing factors to the cost reduction. We expect higher patient satisfaction, as both hospital stay and time-to-work are shorter and side effects such as nausea are reduced. However, both safety and effectiveness – including the necessity for re-intervention due to incomplete resection- have not yet been fully evaluated. In summary, we expect comparable effectiveness of the procedure in a safe and patient friendly environment whilst achieving a significant cost reduction.

**USUAL/STANDARD CARE:** The Dutch Guideline 'Heavy menstrual bleeding' (NVOG: Dutch Society of Obstetrics and Gynecology) recommends hysteroscopic myomectomy as treatment of first choice in case of symptomatic submucous myomas [19]. In the current situation, patients are admitted into daycare and they are operated under general anesthesia. This requires an operating room with a full anesthetic team. Postoperatively, patients are transferred to the recovery unit from which they go back to the ward. Several hours later discharge follows. Procedural sedation has never been evaluated for hysteroscopic myomectomy regarding (cost)effectiveness. The guideline committee suggests that local anesthesia or 'conscious sedation' can be taken into consideration for hysteroscopic myomectomy based on indirect evidence from other areas in healthcare [19].

## **Relevance**

**THE INTERVENTION TO BE INVESTIGATED:** Hysteroscopic myomectomy for symptomatic type 0 or I submucosal myomas in an outpatient setting using procedural sedation with propofol compared to hysteroscopic myomectomy in an inpatient clinical setting using general anesthesia. According to the guidelines from the Health Care Inspectorate (IGZ) and Dutch Institute for Healthcare Improvement (CBO) procedural sedation is administered by a qualified sedation practitioner with standard monitoring.

**EXISTING EVIDENCE OF EFFECTIVENESS:** Due to proved safety, higher patient satisfaction, shorter procedure time and faster recovery the use of propofol in sedation practice has increased [11-12; 20]. Analogue to the successful shift of diagnostic procedures to an office-based setting [21-22], hysteroscopic myomectomies can be moved away from the operating theatre when adequate sedation and analgesia is secured. In a systematic review we found two studies evaluating feasibility and patient satisfaction with gynaecological surgery under procedural sedation [23-24]. From these studies, sedation with propofol/alfentanil seems to be feasible for endometrial balloon ablation and prolaps surgery.

In a second systematic review we evaluated the outcome of hysteroscopic resection of type 0 and type 1 myomas. The results of hysteroscopic removal of type 0/1 are very good with complete removal up to 100% and successful reduction of menstrual bleeding. The risk of complications is low (3,2% in a prospective bipolar resection trial of 449 patients) [25].

In summary, the systematic review evidence suggests that 1. procedural sedation anesthesia is feasible and well-tolerated in gynaecological surgery; and 2. hysteroscopic myomectomy is a safe and technically successful procedure. However, there are no randomised efficacy data.

**INNOVATIVE CHARACTER:** The proposed RCT is the first trial comparing the use of PSA in hysteroscopic myomectomy compared with the current standard hysteroscopic myomectomy in an inpatient setting under general anesthesia.

**RELEVANCE FOR PRACTICE:** The Dutch Guideline 'Heavy menstrual bleeding' recommends hysteroscopic myomectomy as treatment of first choice in case of symptomatic submucous myomas. In the current situation, patients are admitted into daycare and they are operated under general anesthesia. Performing hysteroscopic myomectomy under propofol sedation will lead to numerous advantages. For the patients direct advantages are a shorter hospital stay, less risk related to general anesthesia, treatment in a patient friendly setting and adequate recovery to pre-procedural functional and physiological level. For the hospital organization it leads to less pressure on surgery waiting lists, more flexible scheduling and a cost-reduction. From a societal perspective a further cost reduction is expected because of faster return to normal activities and shorter absence of work.

**ANTICIPATED COST-EFFECTIVENESS:** With an incidence of 3000 myomas eligible to resect in an office setting annually, and an estimated cost saving of €595 per resection, an estimated cost reduction of almost 1,8 million euros can be expected from a healthcare perspective annually. When taking cost savings due to reduced productivity losses into account, the savings are around 2,8 million euros annually from a societal perspective. Not unimportant to add is that we expect this cost-reduction at a concurrent improvement in patient satisfaction and quality of life.

**IMPLEMENTABILITY:**

The Dutch Society of Obstetrics and Gynecology (NVOG) acknowledged the research question as an important knowledge gap, prioritized the project and agreed on adjustment of guidelines after proven (cost-)effectiveness. The strategy will be imbedded in the guideline

'Hevig menstrueel bloedverlies' and model protocol 'Submuceuze myomen, diagnostiek and behandeling'. Beyond the scope of this research protocol, other gynaecological procedures (e.g. endometrial ablation) performed under general anesthesia for reasons of anxiety or pain perception can be performed under procedural sedation. This would lead to a further cost reduction besides offering a patient friendly treatment mode.

## 2. OBJECTIVES

**Primary Objective:** To demonstrate non-inferiority of complete hysteroscopic resection of submucous myomas under procedural sedation with propofol compared to hysteroscopic resection under general anesthesia.

**Secondary Objective(s):** To compare the cost effectiveness, pain, menstrual blood loss (PBAC score), quality of life, return to daily activities/work, hospitalization, (post)operative complications, re-interventions for hysteroscopic resection of submucous myomas under procedural sedation with propofol and for resection under general anesthesia.

**Specific questions:**

1. Does the use of procedural sedation for hysteroscopic myomectomy lead to a comparable same rate of complete resections, as compared to using general anesthesia?
2. What is the generic and specific quality of life measured with the Uterine Fibroid Symptom and Quality of Life questionnaire (UFS QoL) [26], EuroQoL (EQ-5D-5L) [27-28] and recovery index (RI-10) [29] after a hysteroscopic myomectomy using procedural sedation versus hysteroscopic myomectomy under general anesthesia?
3. What is the cost-effectiveness of hysteroscopic myomectomy using PSA versus hysteroscopic myomectomy under general anesthesia?

### 3. STUDY DESIGN

**Study design:** We aim to conduct a multicenter randomized non-inferiority trial comparing procedural sedation with general anesthesia in patients with symptomatic submucosal type 0 or I myomas up to 3 centimetres in diameter scheduled for hysteroscopic myomectomy. A cost-effectiveness study will be performed alongside the clinical study.

**Setting:** The proposed study will be performed within a consortium of university and teaching hospitals in the Netherlands. Patients will undergo hysteroscopic myomectomy either under general anesthesia or procedural sedation with propofol.

**Duration:** Preparation (6 months): protocol, database, approval medical-ethics committees. Inclusion (24 months): 205 patients. Follow-up (12 months): postoperative revision, recovery, complications. Analysis (6 months): data-analysis, publication.

## **4. STUDY POPULATION**

### **4.1 Population (base)**

We will study women with a minimum age of 18 years with a maximum of 2 symptomatic type 0 or I submucous myomas with a maximum diameter of 3 cm. They should be American Society of Anesthesiologist class 1 or 2 and able to sufficiently speak Dutch to fully understand the study and to complete the questionnaires.

### **4.2 Inclusion criteria**

In order to be eligible to participate in this study, a subject must meet all of the following criteria:

- Minimum age: 18 years
- Symptomatic type 0 or I submucous myomas
- Maximum number of myomas: 2
- Maximum diameter of submucous myomas: 3 cm
- American Society of Anesthesiologist class 1 or 2

### **4.3 Exclusion criteria**

A potential subject who meets any of the following criteria will be excluded from participation in this study:

- Aged under 18 years
- Inability to understand Dutch
- American Society of Anesthesiologist class 3 or 4
- Clotting disorders
- Severe anemia (Hb under 5.0 mmol/l).

### **4.4 Sample size calculation**

The study is designed as a non-inferiority study, in which we want to investigate if hysteroscopic myomectomy under procedural sedation with propofol is non-inferior to the same surgical procedure under general anesthesia. With 205 women randomized we have 90% power to demonstrate non-inferiority, based on an estimated 2,5% incomplete resections in both groups, with an non-inferiority upper limit of 10% incomplete resections defined as non-inferior (i.e. a delta of 7.5%), an alpha of 0.025 and a drop-out rate of 10%.

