### **6.2 Randomisation, blinding and treatment allocation**

Randomisation will be performed web based through Alea with the use of a block design, with a variable block size. The expertise for this technology is already available for the study group (obs/gyn consortium). The study will not be double-blinded, as it is impossible to blind the health care workers and patients involved for the strategy to which the woman is allocated. The person performing the transvaginal ultrasonography at six weeks follow up, however, will be blinded for the study arm and judgement of completeness by the surgeon during the procedure. Patients will be able to complete the questionnaires online, through an link they receive by e-mail. In case patients wish to complete the questionnaires on paper, the research nurse will send the questionnaires by post at the follow-up moment.

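### 205 women do not give 90% power at alpha 0.025: exact power is about 74% after the planned drop-out, and no test that holds alpha reaches 90%

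*Protocol*

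**What the plan says.** Section 4.4 sizes the trial in one sentence. It claims: "With 205 women randomized we have 90% power to demonstrate non-inferiority, based on an estimated 2,5% incomplete resections in both groups". It sets the upper limit for incomplete resections at 10%, which it translates into a delta of 7.5 percentage points, and adds "an alpha of 0.025 and a drop-out rate of 10"%. The Summary repeats the result: "with an non-inferiority upper limit of 10%, 205 women are needed".

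Section 4.4 does not name the test or interval to which the 90% refers. It does not say whether alpha is one-sided, and no allocation ratio is given; section 6.2 says only that randomisation is done "with the use of a block design, with a variable block size". Section 8.1 plans relative risks with a 95% confidence interval and a chi-square or Fisher test. It names no interval for the 7.5-point difference on which the trial was sized.

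**The concern.** With 92 evaluable women per arm and a 2.5% event rate, each arm is expected to have 92 × 0.025 = 2.3 incomplete resections. The normal approximation to a difference in proportions is poor at counts this small. It also takes its variance from equal rates of 2.5%. At the margin, where type I error has to be controlled, the rates are 10% and 2.5% and the variance is more than twice as large. A sample size from that formula can therefore fall well short of its stated power once a method that holds alpha is used.

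What is at stake is the primary conclusion. If the analysis holds alpha, the trial is much more likely to be inconclusive than the sponsor believes. If the analysis is chosen to match the sizing formula, false claims of non-inferiority become nearly twice as frequent as the stated alpha.

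**Working it through.** **Inputs (section 4.4).** True rate 2.5% in both arms; margin 0.075; alpha 0.025; power 90%; drop-out 10%. Assumed: 1:1 allocation and one-sided alpha. A two-sided 0.025 would need 108 per arm, which does not lead to 205.

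**1. The protocol's own figure.**
n per arm = (1.960 + 1.2816)² × 2 × 0.025 × 0.975 / 0.075² = 91.06, so 92.
2 × 92 = 184 evaluable; 184 / 0.9 = 204.4, so 205 randomised.
The figure reproduces. The approximate power of the same formula at 92 per arm is 90.3%.

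**2. Why the formula fails.** Per-woman variance of the difference:
- at 2.5% and 2.5%: 2 × 0.025 × 0.975 = 0.0488
- at 10% and 2.5%: 0.10 × 0.90 + 0.025 × 0.975 = 0.1144

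The ratio is 0.1144 / 0.0488 = 2.3.

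**3. Exact power and type I error.** All pairs of event counts were enumerated with their binomial probabilities. Non-inferiority is claimed when the upper limit of the two-sided 95% interval for the risk difference is below 7.5 points. Results for 92 per arm:

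| Interval | Power at 2.5% in both arms | Type I error at 10% vs 2.5% | Maximum type I error, control rates up to 15% |
|---|---|---|---|
| Wald | 89.1% | 4.5% | 7.7% |
| Wald, continuity-corrected | 80.6% | 2.1% | 3.3% |
| Agresti-Caffo | 83.3% | 2.9% | 3.4% |
| Newcombe | 73.6% | 2.1% | 2.6% |
| Farrington-Manning | 73.6% | 2.1% | 2.6% |
| Miettinen-Nurminen | 73.6% | 2.1% | 2.4% |

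Only the last three hold alpha at or very near 2.5% throughout. If all 205 women are evaluable (103 and 102), these three give 81.2%. Wald then gives 91.0%, with type I error 3.9% at 10% vs 2.5%.

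**4. Could another method recover 90%?** Any valid test must hold 0.025 at every point on the margin. The most powerful test against one such point therefore bounds the power of all valid tests. The tightest bound found uses a control rate of 1.3% (8.8% under sedation). It is 78.7% at 92 per arm and 83.6% at 103 and 102. So no valid test reaches 90%, even without drop-out.

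**5. Size that would deliver 90%.** A score interval stays at or above 90% from about 133 evaluable per arm: 266 / 0.9 = 295.6, so about 296 randomised. The asymptotic Farrington-Manning formula gives 140 per arm: 280 / 0.9 = 311.1, so 312.

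**6. Sensitivity to the event rate.** Newcombe, 92 per arm, same true rate in both arms:

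| True rate | 1.0% | 1.5% | 2.5% | 5% | 7.5% |
|---|---|---|---|---|---|
| Power | 88.0% | 82.6% | 73.6% | 56% | 45% |

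**7. What this means for a result.** With 92 per arm, 3 incomplete resections under sedation against 2 under general anaesthesia gives a Newcombe upper limit of 7.2 points, which passes. With 4 against 2 the Newcombe limit is 8.7 points, which fails, while the Wald limit is 7.3 points, which passes. One additional event decides the trial, and at 4 against 2 the choice of interval decides it.

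**The case against.** The strongest reply is that nothing was miscalculated. The number comes from a standard sizing formula, and exact power below nominal at low event rates is a known limitation of that formula. This is right about the arithmetic, and the criticism is of the method. The shortfall, however, is about 16 percentage points (90 − 74), far more than rounding.

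Second, the protocol never commits to a Wald interval. With equal assumed rates the pooled and unpooled variances are the same, so 205 does not show that a Wald analysis was intended. This stands. The 4.5% describes what would follow if the analysis matched the sizing formula, at one point on the margin; it is not a property of a declared analysis.

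Third, 74% is itself conditional. It assumes the full 10% drop-out, and exact power moves in a saw-tooth, from about 69% to 76% for 88 to 96 evaluable women per arm. With everyone evaluable it is about 81%. Lower event rates, which section 1 makes plausible by citing complete removal in up to 100%, give more power: 88.0% at 1.0% with 92 per arm, and above 90% with 102 per arm at 1.5% or lower. These are fair qualifiers and belong in the restated text. But section 4.4 makes its claim at 2.5% with 10% drop-out, and there no valid method supports it.

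Fourth, the choice of interval is often left to the SAP. That is reasonable in general, but a power figure has no meaning without the decision rule to which it belongs.

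**Conclusion.** The concern holds. At the protocol's own inputs, 205 randomised women (184 evaluable) give about 74% exact power with intervals that keep alpha at or close to 0.025, and about 81% if nobody drops out. The bounds of about 79% and 84% show that 90% is out of reach for any valid test at this size. The chance of missing true non-inferiority is about 1 in 4, against the 1 in 10 stated. Keeping roughly 90% power through a Wald interval would raise the false-claim rate to 4.5% at 10% vs 2.5%.

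The conclusion rests on 1:1 allocation, a one-sided alpha of 0.025 (the reading that reproduces 205) and a decision based on the absolute risk difference.

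**What to change.** In section 4.4, remove the 90% claim and name the interval that decides non-inferiority: a Newcombe or Miettinen-Nurminen 95% interval for the risk difference, with its upper limit compared with 7.5 points. State the allocation ratio and that alpha is one-sided. Suggested wording:

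*With 205 women randomised 1:1 and 10% drop-out (184 evaluable), exact power at a one-sided alpha of 0.025 is about 74% if 2.5% of resections are incomplete in both arms (about 81% if all 205 are evaluable), and about 56% if the rate is 5% in both arms. Non-inferiority is concluded if the upper limit of the two-sided 95% Newcombe interval for the risk difference is below 7.5 percentage points.*

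The sponsor may add a lower rate for balance, for example 88.0% power at a 1.0% rate with 184 evaluable. The Summary should be brought into line, since it says that 205 women are needed without giving the power on which that rests.

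The cost is a less favourable stated figure. The change is to wording only and requests no increase in enrolment. Should the sponsor wish to keep 90% power at these inputs, about 296 women would have to be randomised.
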